# Comparison of tonic spinal cord stimulation, high-frequency and burst stimulation in patients with complex regional pain syndrome: a double-blind, randomised placebo controlled trial

**DOI:** 10.1186/s12891-015-0650-y

**Published:** 2015-08-25

## Abstract

**Background:**

Complex Regional Pain Syndrome (CRPS) is a disabling disease that is sometimes difficult to treat. Although spinal cord stimulation (SCS) can reduce pain in most patients with CRPS, some do not achieve the desired reduction in pain. Moreover, the pain reduction can diminish over time even after an initially successful period of SCS. Pain reduction can be regained by increasing the SCS frequency, but this has not been investigated in a prospective trial. This study compares pain reduction using five SCS frequencies (standard 40 Hz, 500 Hz, 1200 Hz, burst and placebo stimulation) in patients with CRPS to determine which of the modalities is most effective.

**Design:**

All patients with a confirmed CRPS diagnosis that have unsuccessfully tried all other therapies and are eligible for SCS, can enroll in this trial (primary implantation group). CRPS patients that already receive SCS therapy, or those previously treated with SCS but with loss of therapeutic effect over time, can also participate (re-implantation group). Once all inclusion criteria are met and written informed consent obtained, patients will undergo a baseline assessment (T0). A 2-week trial with SCS is performed and, if successful, a rechargeable internal pulse generator (IPG) is implanted. For the following 3 months the patient will have standard 40 Hz stimulation therapy before a follow-up assessment (T1) is performed. Those who have completed the T1 assessment will enroll in a 10-week crossover period in which the five SCS frequencies are tested in five periods, each frequency lasting for 2 weeks. At the end of the crossover period, the patient will choose which frequency is to be used for stimulation for an additional 3 months, until the T2 assessment.

**Discussion:**

Currently no trials are available that systematically investigate the importance of variation in frequency during SCS in patients with CRPS. Data from this trial will provide better insight as to whether SCS with a higher frequency, or with burst stimulation, results in more effective pain relief.

**Trial registration:**

Current Controlled Trials ISRCTN36655259

## Background

Complex Regional Pain Syndrome (CRPS) is defined as a collection of locally appearing painful conditions following a trauma, which mainly occurs distally and exceeds in severity and duration the expected clinical course of the original trauma; this often results in considerably restricted motor function and is characterised by a variable progression over time [1]. The diagnosis of CRPS in the acute phase is made with the aid of the new criteria of the International Association for the Study of Pain (IASP). These criteria have a high sensitivity of 0.99 and a much improved specificity of 0.79 compared with the previously used diagnostic criteria, such as the Veldman criteria and the Orlando criteria [2–4].

The natural course of the disease is not always favourable, even with a multidisciplinary approach and the use of evidence-based guideline-supported treatment algorithms. CRPS has an estimated incidence of 5.46–26.2 per 100,000 person years (95 % CI: 23.0–29.7) [5, 6] and a prevalence of 20.57 per 100,00. Women are affected more frequently than men (with a ratio of 3.4–4.0:1) and CRPS occurs more often in the upper extremities [5, 6]. The main initiating cause is a fracture, but other traumatic or spontaneous onsets are well documented [3, 5].

Although the pathophysiology of CRPS is incompletely understood, several mechanisms are proposed to contribute to this disease such as inflammation, vasomotor dysfunction, and involvement of the central nervous system with features of central sensitisation and neuroplasticity [7].

Some patients with diagnosed CRPS are unresponsive to any conventional therapy, such as physical therapy, medication and invasive interventions such as sympathetic blockade. In these cases there is a clear indication for spinal cord stimulation (SCS) as a last resort therapy to reduce pain. SCS has been performed in many CRPS patients and has shown an evident and clinically relevant pain reduction that can be maintained for a prolonged period of time [8–12].

The exact mechanism of action that occurs during SCS, which results in pain relief, has not been fully elucidated. However, it is known that for neuropathic pain in general, SCS decreases the hyperexcitability of the multimodal wide dynamic range neurons (WDR), increases the release of gamma-aminobutyric acid (GABA) in the dorsal horn and, subsequently, decreases the release of glutamate. Other mechanisms proposed to be involved are activation of an inhibitory descending pathway and involvement of the cholinergic system. Several CRPS-specific mechanisms of SCS are considered to play a pivotal role, such as inhibiting the hyperexcitable central neural circuitry, a decrease in the efferent-sympathetic output and by antidromic activation which, in turn, causes the release of several vasoactive substances, such as nitric oxide, substance P and calcitonin gene-related peptide [13–15].

However, despite these successes some CRPS patients are not responsive or, in others, the pain-reducing effect diminishes over time due to tolerance [9–12]. It is suggested that pain relief in some of these tolerant non-responsive patients can be recaptured by increasing the SCS frequency to 250 Hz and beyond [16]. Also, burst SCS is a novel stimulation modality that can reduce pain, but has not yet been investigated in patients with CRPS [17, 18]. Further research is needed to gain more insight into the (patho)physiological mechanisms of CRPS and to elucidate the effects of SCS when stimulating with different frequencies and waveforms.

### Aim

This study aims to compare the effects of five different SCS modalities in patients with CRPS and determine which frequency is most effective in terms of pain reduction; these frequencies are standard stimulation with 40 Hz , 500 Hz, 1200 Hz, burst and placebo stimulation.

## Methods

### Study design

This is a prospective randomised, double-blind and placebo-controlled crossover trial. The study is a multi-centre trial including one university hospital and four regional hospitals located throughout the Netherlands. Figure 1 provides an overview of the study and Fig. 2 a detailed overview of the crossover trial.

**Fig. 1 Fig1:**
[figure not shown]
Flowchart of the entire study

**Fig. 2 Fig2:**
[figure not shown]
Detailed flowchart of the crossover period

### Study population

Patients considered for enrollment in this trial must be diagnosed with CRPS that is in accordance with the endorsed IASP criteria at the time of disease onset. We defined two groups of patients that can take part in this trial. The first group (primary implantation group) consists of patients with chronic CRPS who are unresponsive to conventional therapies (e.g. pharmacologic treatment, interventional blockade of the sympathetic nervous system, or physical therapy aimed at increasing or regaining functionality by training programs). The second group (re-implantation group) consists of patients who already have SCS therapy, or were treated with SCS in the past but with loss of therapeutic effect over time. In the re-implantation group it is imperative that the paresthesia, that is or was felt under SCS therapy, has adequate overlap with the painful area.

### Inclusion and exclusion criteria

Eligibility for SCS is in accordance with the Dutch CRPS and Neuromodulation Guidelines. These guidelines state that patients must have a mean pain intensity of a least 5, as measured on a visual analogue scale (VAS; range 0–10), a CRPS duration of at least 12 months, and no lasting success or complications with conventional therapy. An additional requirement for this study is that the CRPS is located in one extremity only. Exclusion criteria are: anticoagulant drug therapy or disturbed coagulation, age < 18 years, pregnancy, ICD or pacemaker, life expectancy < 1 year, lack of cooperation of the patient, drugs, medication or alcohol addiction, and immune-compromised patients.

### Ethical approval

Approval from the Medical Ethics Committee of Erasmus Medical Center Rotterdam was obtained in August 2011 (Registration number: MEC-201 1-012). The trial was subsequently registered in the Current Controlled Trials register (ISRCTN 36655259). Written informed consent is obtained from all patients before enrollment into the trial.

### Primary outcome parameters

The main study parameters are pain reduction and patient satisfaction. The pain scores are measured with the McGill Pain Questionnaire-Dutch Language Version (MPQ-DLV) [1, 19] and a 4-day VAS diary measurement is used to monitor pain intensity during the morning, afternoon and evening. The Global Perceived Effect (GPE) is measured by two questions on a 7-point Likert scale [9]. The VAS score is considered the main primary outcome parameter out of these three. All questionnaires are completed by the patient.

### Secondary outcome parameters

Secondary outcomes consist of detecting temperature asymmetry by using video thermography imaging [20–27], and electrical quantitative sensory testing (e-QST) together with the conditioned pain modulation (CPM) [28–32]. Current Perception Threshold (CPT), Pain Perception Threshold (PPT) and Pain Tolerance Threshold (PTT) are measured with e-QST and provide more insight into the disease characteristics, such as hyperalgesia, hypoalgesia and allodynia. The CPM paradigm will provide further details on the patient’s pain suppression system.

A MicroFet Dynamometer® is used to measure muscle strength of the flexors and extensors of the elbow in case of the upper extremity, and of the knee and the foot in case of CRPS in the lower extremity. The grip strength and the pinch strength is determined by means of a Jamar Hydraulic Hand Dynamometer® and a Jamar Hydraulic Pinch Gauge®, respectively. The pinch strength is measured in two ways: thumb tip to index fingertip, and thumb pad to lateral aspect of middle phalanx of index finger; the biceps and the triceps. In addition, a walking test is performed only in patients that have lower extremity CRPS. This test records how long it takes to cover a 10 m distance when walking at a comfortable and maximum walking pace. Furthermore, the maximum walking distance is assessed during a 2-min walk where the patient is instructed to cover as much distance as possible within these 2 min [33–40].

The types of activity and physical activity level (PAL) of a patient is continuously measured with the VitaMove system (2 M Engineering, The Netherlands) for multiple days (2–3 day), providing a detailed and continuous report on the patient’s energy expenditure, motions and postures over the course of several days [41–46]. This device is capable of interpreting various positions like sitting, standing and lying down as well as discerning various activities like walking, running, cycling or general motion of the arms, legs and trunk. The PAL can be estimated with the VitaScore software that calculates the energy expenditure with the aforementioned activities and the patients characteristics like weight, height, age and sex to estimate the basal metabolism. The energy expenditure can provide information on the level of activity of a patient that ranges from extremely inactive-extremely active.

Artificial skin blisters are created to measure whether local inflammation is still present in these patients before SCS and the effects stimulation therapy might elicit on the inflammatory profile [47–56]. A blood test is performed to assess the outcome of the endogenous opioids (such as dynorphin, endorphin and encephalin) before and after SCS [57–59]. An additional consent must be signed by the patient in order to perform both the blood and artificial skin blisters test.

Multiple questionnaires are filled in by the patient throughout the course of the study to monitor the various dimensions (Table 1). These include *psychological and social evaluation:* Inventory for Social Support (ISS) [60], Pain Catastrophizing Scale Dutch Version (PCS-DV) [61–63], RAND-36 [64–66], the Hospital Anxiety and Depression Scale (HADS) [67, 68] and the Tampa Scale for Kinesiophobia (TSK) [69, 70]. *Physical activity:* the Disabilities of Arm Shoulder and Hand Questionnaire (DASH) [42, 71, 72] when the upper extremity is affected, and the Walking Ability Questionnaire when the lower extremity is affected [73–75]. *Economic evaluations:* The cost analysis is performed from a societal viewpoint in collaboration with the Institute for Medical Technology Assessment of Erasmus University Rotterdam. Three categories of costs are distinguished: 1) Direct costs within the healthcare system, 2) Direct costs outside the healthcare system, and 3) indirect costs outside the healthcare system. These data are collected using diaries and the Trimbos/iMTA questionnaire for Costs associated with Psychiatric Illness (TiC-p) and health consumption, simultaneously with the clinical data and quality of life data. The costs are valued using the Dutch guidelines for cost analysis in healthcare (Health Care Insurance Board).

**Table 1 Tab1:** Data collection overview throughout the entire study

	T0	T1	C1	C2	C3	C4	C5	C6	T2
*Medical History*	x								
*Physical examination*	x	x							x
*Stimulation evaluation*		x	x	x	x	x	x		x
*Pain diary*	x	x	x	x	x	x	x		x
*McGill Pain Questionnaire*	x	x	x	x	x	x	x		x
*Global Perceived Effect*		x	x	x	x	x	x		x
*Final assessment frequency chosen*								x	
*HADS*	x	x							x
*RAND-36 / SF-36*	x	x							x
*PCS*	x	x							x
*ISS*	x	x							x
*TSK*	x	x							x
*DASH*	x	x							x
*Walking Ability Questionnaire*	x	x							x
*Prodisq A-E*	x	x							x
*TiC-p and Healthcare consumption*	x	x							x
*Thermographic imaging*	x	x							x
*Muscle strength*	x	x							x
*Walking Test (if applicable)*	x	x							x
*QST*	x	x							x
*CPM*	x	x							x
*Blood and Blister test (optional)*	x	x							x
*Physical activity monitoring*	x	x							x

Productivity costs: The productivity costs are defined as the costs of absence from paid work due to CRPS, including the impact of compensation mechanisms, the cost of efficiency losses (productivity costs while working at a slower pace) and the costs of hindrance at unpaid work. For this, the three modules of the PRODISQ questionnaire for measuring and valuing productivity costs for unpaid work are used [76, 77]. For costs related to unpaid work we use a module of the Health and Labour Questionnaire (HLQ) [78]. For the valuation of productivity losses, the friction cost method is used, taking into account that in a production process everyone is replaceable after a certain period (the so-called friction period). For the valuation of each hour of productivity lost (and the length of the friction period) we use the guidelines as presented in the costing manual [79].

Medication consumption is assessed by taking an inventory of all (pain)medication and dosing the patients use at the time of the T0, T1 and T1 assessment. The pain medication will be stratified into the various medication groups and a the sum dosage of the various pain medication groups will be calculated.

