### Sample size calculation

By means of MANOVA for repeated measurements within factors, the potential differences in effect of the five different stimulation modalities will be assessed. A minimal detectable effect size (f) of 0.15 on the main primary outcome parameter pain intensity (VAS) was chosen. The required minimum number of participating patients is negatively associated with the correlation between measurements during the cross-over. Unfortunately, no data of previous research on this correlation were available at the time of setting up this study. Therefore, we made an conservative guess and a correlation of 0.6 was chosen. Thus, assuming a power of 0.8 and a significance level (σ) of 0.05 , an a priori sample size of 48 is required.

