### Follow-up measurement T2

The T2 assessment is performed when a patient has completed the 3-month period with the frequency of choice. This T2 evaluation enables us to compare all the primary and secondary outcomes parameters with the T1 assessment with standard SCS and the baseline T0 assessment prior to SCS therapy. The patient is actively asked whether they want to continue with the SCS program they have chosen, or want to switch to another one based on the crossover results.

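### Analgesic use is scored as summed dosage per medication group with no common unit, so a drug switch at unchanged analgesic effect can appear as a rise or fall in consumption

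*Protocol article*

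**What the plan says.** The rule is in the last paragraph of the protocol article's section on secondary outcome parameters. The raw data are drug and dose for each patient: "Medication consumption is assessed by taking an inventory of all (pain)medication and dosing the patients use". The inventory is taken at three main assessments, given as T0, T1 and a second T1, which is evidently a slip for T2.

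The score is then built in two steps. First, "The pain medication will be stratified into the various medication groups". Second, "the sum dosage of the various pain medication groups will be calculated". The groups are not listed and no unit is given. No section mentions a morphine equivalent, a defined daily dose or any other weighting.

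The section on the T2 follow-up says that this visit makes it possible to "compare all the primary and secondary outcomes parameters with the T1 assessment with standard SCS and the baseline T0 assessment". Medication consumption is described among the secondary outcomes, so it enters this comparison within patients. The statistical analysis section plans mixed linear models for the outcomes, with results shown as mean and standard deviation.

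**The concern.** Adding dosages is sound only if one unit of every drug in a group represents the same amount of analgesia. Otherwise the score reflects which drug is taken as well as how much is used. A patient moved to a drug that is more potent per unit dose would be recorded as having cut consumption, and a patient moved the other way as having raised it, with no change in analgesic effect in either case.

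Between T0 and T2 a patient passes through the trial stimulation, three months of 40 Hz, a 10-week crossover and three further months on the chosen setting. A change of drug in that time is possible, and under the stated rule it would enter the comparison as a change in consumption. What is at stake is whether the reported change in analgesic use, in size and possibly in direction, describes consumption or drug substitution.

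**Working it through.** **Is there a figure to reproduce?** Not for this outcome: the article gives no number for medication consumption. Its one recomputable design figure, the sample size of 48, rests on the VAS and plays no part here.

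**Inputs**
- Scoring rule: sum of dosage within a medication group (secondary outcome parameters).
- Comparison: T2 against T1 and T0 within patients (T2 follow-up section).
- Potency ratio k between two drugs of one group, per unit dose: not in the documents. Assumed range 1 to 10.
- Share s of a patient's summed group dose that is switched: not in the documents. Shown for s = 1 (all of it) and s = 0.5 (half).

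**Formulas.** Let the group score before the switch be D. At equal analgesic effect, the switched part sD becomes sDk with the weaker drug and sD/k with the stronger one. The relative change in the score is therefore
- to the weaker drug: (1 - s) + s·k - 1 = s(k - 1)
- to the stronger drug: (1 - s) + s/k - 1 = -s(1 - 1/k)

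**Results for the unconverted sum**

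| k (assumed) | Full switch, to weaker | Full switch, to stronger | Half switched, to weaker | Half switched, to stronger |
|---|---|---|---|---|
| 1 | 0% | 0% | 0% | 0% |
| 1.5 | +50% | -33% | +25% | -17% |
| 2 | +100% | -50% | +50% | -25% |
| 5 | +400% | -80% | +200% | -40% |
| 10 | +900% | -90% | +450% | -45% |

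For example, at k = 5 a full switch gives 5 - 1 = 4, or +400%, in one direction and -(1 - 1/5) = -0.80, or -80%, in the other.

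The two directions are not symmetric. A switch to the weaker drug can raise the score without limit as k grows, while the opposite switch cannot lower it by more than 100%. Equal numbers of switches each way therefore need not cancel in a mean.

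**After conversion.** If each dose is multiplied by its potency before summing, the switched part is k times larger in dose and k times smaller in weight. The product is unchanged, so the change is 0% for every k and s. If the table uses a ratio c that differs from the true k, a full switch to the weaker drug leaves k/c - 1. With k = 2 and c = 1.5 that is 2/1.5 - 1 = +33%, against +100% without conversion. The unconverted sum is the case c = 1 for every pair of drugs.

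**The case against.** The strongest reply is that the text is under-specified and has not been shown to be wrong. It does not say that milligrams are added, and the groups might be narrow enough to hold drugs of similar potency. A journal article condenses a fuller protocol, and units and conversion tables are commonly left to that document or to the analysis plan. This stands in part: a conversion may exist elsewhere, and the size of any distortion cannot be known from this text. But the article does not merely omit a detail. It states the operation, a sum of dosages, and followed as written that operation gives the results above whenever k differs from 1. If a conversion is applied, the sentence misdescribes the score and still needs correcting.

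It can also be said that drug and dose are recorded individually, so equivalents can be computed later. That is right, and it is why the fix is cheap. It does not settle which conversion will be used, and that is better fixed before the results are seen.

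Three stronger readings are tempting and are not supported.
- A reader might infer that every change of drug within a group produces a large artefact. It can do so only where the two drugs differ clearly in potency, and the documents give no drugs, doses or switching rates.
- A reader might infer that one switch would cancel true reductions in many other patients. At k = 10, a switch from 1 unit to 10 adds 9 units. If the others also start at 1 unit, a true 50% reduction saves 0.5 each, so 9/0.5 = 18 patients are offset. If they take the weaker drug at an equi-effective dose they start at 10, save 5 each, and 9/5 = 1.8 are offset. The starting doses are unknown, so no such count should be relied on.
- A reader might infer that the outcome is needed to interpret the VAS. The article does not give it that role. The medication inventory belongs to the main assessments, not to the crossover periods.

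**Conclusion.** The point holds as a defect in the definition of one secondary outcome. As written, the score can register a drug switch at unchanged analgesic effect as a change in consumption between T0, T1 and T2. For a full switch the distortion of that patient's group score runs from none at k = 1, through +100% or -50% at k = 2, to +900% or -90% at k = 10. It is half as large if half the dose is switched.

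This rests on three assumptions: that dosages are summed without conversion, as the text reads; that a group contains drugs of unequal potency; and that some patients change drug between assessments. The effect on the group mean cannot be quantified from the documents.

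I have read the rule as a sum within each group. If it means a single sum across groups, comparability is weaker still. The before-after comparison alone is affected. The randomised crossover comparison of the five modalities on VAS, and the sample size, are untouched. The correction should be made, but the main result does not depend on it.

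**What to change.** Replace the summed dosage with a sum of standardised doses:
- List the medication groups. Within each, convert every drug to a common unit before summing: oral morphine equivalents for opioids and defined daily doses for the other groups. Take the factors from one published table, named and fixed before analysis.
- Where no accepted conversion exists, report the drugs separately or as use or no use.
- For each group, also report the proportions of patients who stopped, reduced, kept or increased it between T0, T1 and T2.
- In the same paragraph, correct the assessment times so that the third reads T2.

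The cost is a sentence or two and a conversion table. No further data collection is needed, because drug and dose are already inventoried. The drawback is that conversion factors are approximate, so some error from switching will remain.
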